## Methods/Design

A randomly-allocated, three-parallel group, time-series design with a social support program serving as the control group will be used to accomplish the aims of the study. Outcome measures will be administered at Weeks 1, 12, and 24. All interventions will involve a 12-week intervention period (three or six teleconference sessions weekly, and four one-to-one phone calls every other week) followed by a 12-week non-contact period to determine whether the effects persist. The design will enable us to compare the overall immediate and sustained outcomes of the three interventions. The protocol is approved by the Cleveland Clinic’s Institutional Review Board (ref: 11-844) in accordance with the Declaration of Helsinki. The study is funded by the National Multiple Sclerosis Society.

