### Sample size

In order to achieve an adequate power of 0.80 to test hypotheses, we will seek to recruit a total of 189 individuals for this study and, more specifically, 63 in each condition. The total number of individuals to be recruited is based on calculations of sample size and power for a balanced repeated-measure mixed effect model with three time points (Weeks 1, 12, and 24) using a formula provided by Hedeker et al.
[33]. We assumed equal variance and correlation (rho = 0.5) between measures across time points, and an effect size of 0.6 at Weeks 12 and 24. These calculations account for 20% attrition over time.

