##### Data management and analysis

A secure online application, Research Electronic Data Capture
[49], will be used to manage recruitment efforts and facilitate data collection. The first step in the analysis process will be to compute summary statistics, calculate outcome scores, and conduct quality control assessments. The second step in the analysis will be to test whether the randomization process resulted in equivalent groups at baseline. If differences are found at baseline, these variables will be used as covariates during the hypothesis testing phase. The third step in the analysis process will be addressing normality assumptions, and the potential for missing data, before hypothesis testing begins. If the normality assumption is violated, then an appropriate data transformation will be used. Missing data will be treated conservatively. If appropriate, maximum likelihood, multiple imputation, or last observation carried forward will be used to estimate the missing values. After addressing issues of attrition and missing data, the fourth step will be to conduct intent-to-treat analysis to test the hypotheses. Linear mixed-effects models will be used as the primary analysis tool for testing hypotheses, which include condition, time, and interactions as the fixed covariates, and a random intercept that models the correlation among outcomes collected from the same subject. The mixed models will allow us to determine whether there are significant differences between the three conditions and whether there are significant differences across time. All tests will be two-sided, and p = 0.05 will serve as the criterion for significance. As is typically the case for mixed-effects analyses, the results will not be controlled for multiple comparisons. The generalized estimating equation approaches will be used if the normality distributional assumption is violated for the random effects in the mixed models. To test for mediation, we will use a linear regression model. This analysis will first involve regressing changes in fatigue impact or physical activity on the intervention conditions, and then regressing changes in fatigue or physical activity on the intervention conditions plus changes in the potential mediator. Mediation will be based on the interventions’ association with physical activity or fatigue impact being reduced in magnitude and non-significant after controlling for the mediator variable.

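### Last observation carried forward, allowed under a promise of conservative handling, is not reliably conservative for the Week 24 test of persistence

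*Protocol article*

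**What the plan says.** In the protocol article, Data management and analysis, missing data belong to the third analysis step and the intent-to-treat mixed models to the fourth, run once attrition and missing values have been dealt with. The governing statement is "Missing data will be treated conservatively", followed by "If appropriate, maximum likelihood, multiple imputation, or last observation carried forward will be used to estimate the missing values". Nothing says which of the three methods applies in which circumstances.

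The hypothesis tests use linear mixed-effects models with condition, time, their interactions and a random intercept. On error rates the section says "All tests will be two-sided, and p = 0.05 will serve as the criterion for significance" and that "the results will not be controlled for multiple comparisons".

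Methods/Design gives the reason for the Week 24 visit: the 12-week intervention is "followed by a 12-week non-contact period to determine whether the effects persist". Sample size plans 63 participants per condition, allows for 20% attrition without giving its timing or its split by arm, and assumes "an effect size of 0.6 at Weeks 12 and 24".

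**The concern.** Week 24 is the only visit that can show whether effects outlast contact with the study team. For a participant lost in the non-contact period, LOCF enters the Week 12 value at Week 24, so the answer to the persistence question is supplied by assumption. For a participant lost before Week 12, it enters the baseline value at both later visits, which implies no change and pulls a real effect towards zero. The direction of the error therefore depends on when people leave and on whether the effect fades. A method with that property cannot be relied on to be conservative.

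The separate fill-in step is also unnecessary. A linear mixed model fitted by likelihood uses every observed value from participants with incomplete follow-up and is valid under missing at random. Maximum likelihood is not a way of filling values in beforehand, although the article lists it as one. After LOCF, the same model treats copied values as if they had been measured.

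At stake are the Week 24 results for the primary outcomes: fatigue impact, self-reported activity and accelerometer activity.

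**Working it through.** **Inputs from the protocol article.** 63 per arm; effect 0.6 SD at Weeks 12 and 24; equal variances and correlation 0.5 between visits; 20% attrition (Sample size). Two-sided 5% tests without multiplicity adjustment (Data management and analysis).

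**Assumptions not in the article.** The timing of dropout, equal loss in the two arms compared, dropout unrelated to outcome, a control arm with no mean change, and how far the Week 12 effect fades by Week 24. Ranges are shown.

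**The plan's own figure.** A two-arm comparison at one visit needs n = 2(1.96 + 0.8416)²/0.6² = 43.6, so 44 per arm. Allowing for 20% loss, 44/0.8 = 55, not 63. The article cites a formula without giving the contrast or the attrition pattern, so this does not show 63 to be wrong, and the point does not depend on it. The stated 63 is used below.

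**What LOCF estimates.** Let e be the share lost before Week 12, l the share lost after it, and d12 and d24 the true effects. Early dropouts contribute no change and late dropouts contribute the Week 12 effect:

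LOCF effect at Week 24 = (1 − e − l) × d24 + l × d12

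Bias = l × d12 − (e + l) × d24

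With d12 = 0.6 and e + l = 0.20:

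| True Week 24 effect | All loss early (e = 0.2, l = 0) | Half and half (e = l = 0.1) | All loss late (e = 0, l = 0.2) |
|---|---|---|---|
| 0 (fully faded) | 0 | 0.1 × 0.6 = 0.06 | 0.2 × 0.6 = 0.12 |
| 0.3 (half faded) | 0.8 × 0.3 = 0.24 | 0.24 + 0.06 = 0.30 | 0.24 + 0.12 = 0.36 |
| 0.6 (persists) | 0.8 × 0.6 = 0.48 | 0.48 + 0.06 = 0.54 | 0.48 + 0.12 = 0.60 |

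With half the loss early, the bias is 0.06 − 0.2 × d24: upward below a true effect of 0.3, zero at 0.3 and downward above it.

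**Rejection rate when the true Week 24 effect is 0.** With correlation 0.5, the change from baseline has variance 2(1 − 0.5) = 1, so the standard error of the contrast is about √(2/63) = 0.178. A mean of 0.12 gives a two-sided rejection probability of 0.103, and a mean of 0.06 gives 0.063. Simulation with 63 per arm (4,000 runs per scenario) agrees:

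- All loss late: 10.1% (t-test on change) and 10.6% (generalised least squares with the covariance taken as known). In a separate run with the planned random-intercept model (20,000 runs), 11.9%.
- Half and half: 6.9% and 5.5% by the first two methods.
- All loss early: 4.6% and 2.6%.

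**The same data without LOCF.** Likelihood analysis of the observed values only (covariance taken as known) gave estimates within 0.01 SD of the true value and rejection of 4.7% to 5.3% in these three patterns when the true Week 24 effect was 0. With a true effect of 0.6, power was 0.87 to 0.88, against the planned 0.80.

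**Unequal late loss.** If 30% of the active arm and 10% of control leave late (assumed), and the effect has fully faded, LOCF gives 0.3 × 0.6 = 0.18 SD, with 17-18% rejection.

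**The case against.** LOCF is only one of three options, governed by a condition of appropriateness, and maximum likelihood, listed first, is in substance the remedy proposed here. A statistical analysis plan, not shown, may already settle the choice. The article's own planning assumption is an effect of 0.6 at both visits; under it LOCF never overstates the Week 24 effect when loss is balanced. All of this stands, and it makes the harm conditional. It does not remove the fault in the text, which offers LOCF as a way of being conservative at a visit meant to test persistence.

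Three stronger readings are tempting, and the documents do not support them.

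- *The plan inflates Week 24 results in favour of the active arms.* This needs LOCF to be chosen, enough of the loss to fall after Week 12, and the effect to fade. The article gives no dropout timing, and early loss pushes the estimate the other way. Nor does it say that the method would be chosen after treatment differences had been seen, only that the step precedes hypothesis testing.
- *LOCF makes the standard error materially too small.* The shortfall found was small: 0.174 against a true 0.182, in the random-intercept model with late loss. In the change-score comparison the two agreed at 0.178. Most of the excess rejection comes from the shifted estimate.
- *The fallback to generalised estimating equations makes matters worse.* The article says "The generalized estimating equation approaches will be used if the normality distributional assumption is violated for the random effects in the mixed models". Unweighted GEE on incomplete data generally needs data missing completely at random, but in the stated order of steps missing values are handled first. GEE after proper multiple imputation is valid under missing at random. No added harm has been shown.

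**Conclusion.** The point holds in conditional form. LOCF is permitted under a promise of conservative handling that it cannot keep: it favours persistence for late dropouts and dilutes a real effect for early ones. If it is used, with 20% balanced loss and a Week 12 effect of 0.6 SD, the error at Week 24 runs from an overstatement of 0.12 SD (effect fully faded, all loss late) to an understatement of 0.12 SD (effect fully persisting, all loss early: 0.48 instead of 0.60). Under full fading, the nominal 5% test rejects between about 5% and about 10-12% of the time.

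These sizes rest on assumed dropout timing, dropout unrelated to outcome and an assumed degree of fading. They are modest when loss is balanced and larger if late loss differs by arm. The change is worth making because a better analysis is already in the plan.

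**What to change.** In Data management and analysis:

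- Delete LOCF and the separate step of estimating missing values before hypothesis testing.
- State that the primary analysis is the planned linear mixed model, fitted by likelihood (REML) to all observed data from all randomised participants, and that it assumes missing at random.
- Name multiple imputation as a sensitivity analysis, for example with delta shifts applied to the imputed values of dropouts, so that departures from missing at random are examined openly.
- If the GEE fallback is kept, say which data it uses. Once the fill-in step is gone it would otherwise meet incomplete data; running it on the multiply imputed data sets avoids that.

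The cost is a few sentences of analysis text and one extra sensitivity analysis. No change to sample size or data collection is needed. For a two-arm contrast with a true effect of 0.6, 63 per arm and 20% loss, simulated power without LOCF is 0.87 to 0.88, so the target in Sample size ("In order to achieve an adequate power of 0.80 to test hypotheses") is still met for that contrast.

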### Intervention procedures

#### Physical activity-only intervention

This intervention will consist of three group teleconference sessions and four one-to-one calls. The overall purpose of the group teleconferencing will be to teach people how to engage in physical activity and set personalized goals to increase physical activity. The overall purpose of the one-to-one telephone calls will be to provide feedback and encouragement on achieving physical activity goals. Participants will first receive the three one-hour weekly group teleconference sessions from a licensed occupational therapist (OT). We selected OTs to deliver the teleconference sessions because of their expertise and training in managing group processes to facilitate behavior change. Participants will also be provided with four 10 to 20-minute, one-to-one, structured, follow-up telephone calls with a graduate assistant every other week. Both the group teleconference sessions and one-to-one follow-up telephone calls will be consistent with goal-setting theory
[38] and increasing self-efficacy using verbal persuasion, teaching how to set measurable and reasonable goals, proving feedback on goals, and using role modeling (e.g., group members sharing stories)
[39].

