#### FM+ intervention

Participants randomized into this intervention will first receive the three goal-setting physical activity teleconference sessions with the OT, and then will receive three additional teleconference sessions on fatigue management principles with the same OT. Thus, participants will receive a total of six group teleconference sessions. The participants will start to receive the four one-to-one calls from the research assistant after the completion of the first three session. For the purpose of this study, we will only teach fatigue management principles that can be integrated into the focus of changing physical activity behavior. This will include topics emphasizing the importance of rest throughout the day, setting priorities, activity analysis and modification, and living a balanced lifestyle. The first FM+ session will focus on teaching the guiding principles of fatigue management, and discussing the fatigue cycle and how inactivity and deconditioning can make fatigue worse. The second FM + section will focus on evaluating priorities, making active decisions, and using rest strategically in order to have adequate energy to engage in physical activity. The third FM + session will focus on teaching participants how to analyze and modify their schedules in order to manage their fatigue and achieve physical activity goals.

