#### Contact-control social support intervention

The contact control group will consist of the same number of contacts as the FM+, i.e., six weekly one-hour teleconference calls with four biweekly one-to-one phone calls. Thus, this condition will allow us to determine whether it is the actual content being taught in the goal-setting physical activity intervention and FM+ intervention that is beneficial, rather than simply the contacts with the OT or social support provided by other group members. The teleconference calls and the one-to-one calls will involve a discussion of topics commonly addressed in support groups. Topics will include information on MS, disease modifying medications, preventive screening, community organizations, nutrition and supplements, cognitive problems, and recognizing symptoms of depression and chronic stress. For the teleconference sessions, participants will be given the opportunity to share problems and provide peer support and solutions for others. For the one-to-one calls, participants will be asked about topics of interest, and the graduate student will gather educational materials and send them to the participant. This information will be the basis for the discussion in the calls. When issues related to fatigue and physical activity are raised, participants will be directed to publically available educational pamphlets. This type of social support group has been used successfully in other clinical trials as a control condition to evaluate the efficacy of fatigue management programs in persons with MS
[40].

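### Treatment is given in teleconference groups, but the stated model and sample size have no group term; any positive within-group correlation makes between-arm standard errors too small

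*Protocol article*

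**What the plan says.** Under Random allocation procedures, individuals are allocated in blocks of three, one to each condition. Treatment is then given in groups in every arm:

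- Physical activity-only: "Participants will first receive the three one-hour weekly group teleconference sessions from a licensed occupational therapist (OT").
- FM+: the same three sessions, then three more with the same therapist. "Thus, participants will receive a total of six group teleconference sessions".
- Contact control: six weekly teleconferences in which "participants will be given the opportunity to share problems and provide peer support and solutions for others".

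The physical activity section also counts on role modelling through members' stories and on comments from other members about each person's goals. The control section treats support from fellow members as a rival explanation for any benefit.

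Under Data management and analysis, the primary model has condition, time and their interactions as fixed effects, "and a random intercept that models the correlation among outcomes collected from the same subject". The generalized estimating equation fallback names no clustering level.

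Under Sample size, the target is power of 0.80 with 189 participants, 63 per arm. The basis is a "balanced repeated-measure mixed effect model with three time points (Weeks 1, 12, and 24"). On correlation, the section says: "We assumed equal variance and correlation (rho = 0.5) between measures across time points". The planned effect is 0.6 at both follow-up visits, and 20% attrition is allowed for. No group size, ICC or design effect is given.

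**The concern.** A subject-level random intercept accounts for one person's three measurements. It does not account for correlation between different people who shared a teleconference group. Each group belongs to one condition, so variation between groups becomes part of the difference between conditions. The stated model leaves that component out.

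Groups form after randomisation, so there is no group effect at baseline. It arises during treatment and enters the Week 12 and Week 24 contrasts that test the hypotheses, and adjusting for baseline does not remove it. At stake are the width of every between-arm interval, the real level of every between-arm test and, if the correlation is large enough, the stated power.

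**Working it through.** **Inputs from the Protocol article.** 63 per arm, effect 0.6 SD, rho 0.5 between time points, 20% attrition, two-sided 0.05, power 0.80.

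**Assumptions, not in the document.** Group size m from 5 to 10; ICC from 0.01 to 0.10, on the scale of the analysed contrast.

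**Step 1: the plan's own figure.** With rho = 0.5 a change score has variance 2(1 − 0.5) = 1, so a change from baseline and a single-time comparison need the same n:

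n = 2(1.96 + 0.8416)² / 0.6² = 43.6, rounded to 44 completers; 44 / 0.8 = 55 per arm.

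This does not reproduce 63, and the formula that the article cites is not available here. Conversely, 63 × 0.8 = 50.4 completers give independent-subjects power of 0.85 by the normal formula; 50 completers give 0.84 by the noncentral t.

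**Step 2: effect of clustering.**

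- Design effect: DE = 1 + (m − 1) × ICC
- Real type I error of the unadjusted test: 2Φ(−1.96 / √DE)
- Power: noncentral t with 50 / DE per arm and d = 0.6

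Example, m = 8 and ICC 0.05: DE = 1 + 7 × 0.05 = 1.35; √1.35 = 1.162; 1.96 / 1.162 = 1.687, so type I error is 9.2%. The effective n is 50 / 1.35 = 37.0, and power is 0.72.

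| m | ICC | DE | Type I error | Power |
|---|---|---|---|---|
| 5 | 0.01 | 1.04 | 5.5% | 0.83 |
| 10 | 0.01 | 1.09 | 6.0% | 0.81 |
| 8 | 0.02 | 1.14 | 6.6% | 0.79 |
| 8 | 0.05 | 1.35 | 9.2% | 0.72 |
| 10 | 0.05 | 1.45 | 10.4% | 0.69 |
| 10 | 0.10 | 1.90 | 15.5% | 0.57 |

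The normal formula with 50.4 completers gives power one to two points higher (0.805 at m = 8, ICC 0.02; 0.736 at m = 8, ICC 0.05).

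**Step 3: attrition inside groups.** If 20% leave, groups of 8 average 8 × 0.8 = 6.4. At ICC 0.05, DE = 1 + 5.4 × 0.05 = 1.27, type I error 8.2%, power 0.75. Groups of 10 average 8; at ICC 0.10, DE = 1.70, type I error 13.3%, power 0.62.

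**Step 4: where power crosses 0.80.** The completers needed are 43.6 (normal) or 44.6 (t). 50.4 / 43.6 = 1.16 and 50.4 / 44.6 = 1.13. At m = 8 these correspond to an ICC of 0.16 / 7 ≈ 0.02 and 0.13 / 7 ≈ 0.02.

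**Step 5: simulation check.** With 50 per arm and a group effect on the change score, the unadjusted test rejected a true null in 6.8% of trials at m = 5, ICC 0.05; 10.1% at m = 10, ICC 0.05; and 16.4% at m = 10, ICC 0.10. With ICC 0 and m = 5 it rejected in 4.6%.

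**Step 6: few groups.** 63 / 10 = 6.3 and 63 / 8 = 7.9, so each arm has about 6 to 8 groups. A valid group-level test then has few degrees of freedom. In the same simulation (50 / 10 = 5 groups per arm, ICC 0.05) it held its level at 4.7% but had power of only 0.56, less than the 0.69 that the design effect alone suggests.

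**The case against.** The strongest reply is that the size is unknown and may be small. There are only three or six group sessions, alongside four individual calls; randomisation is individual; and Week 24 follows twelve weeks without contact. At ICC 0.01 the type I error is 5.5% to 6.0%, which is minor. This stands: the omission is in the document, but its size is not.

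A reader might infer that the stated power of 0.80 is plainly overstated. The documents do not support that. The standard formula gives about 0.84 to 0.85 at the planned size, so there is slack up to a design effect of about 1.13 to 1.16. Only if the cited formula returned exactly 0.80 would any positive ICC break the claim, and that cannot be checked here.

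A reader might also fault the single random intercept for imposing one correlation across Weeks 1, 12 and 24. That matches the equal-correlation assumption in the sample size section, and nothing in the document indicates that correlation decays. It is not part of this point.

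Finally, the article is condensed and the full analysis plan could contain a group term. That is possible. But the article does spell out the fixed effects and the random term, and the sample size basis has no group component either, so the model as stated is incomplete.

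**Conclusion.** The point holds in conditional form. Delivery is in interacting groups in all arms, and neither the stated model nor the sample size allows for it. With any positive ICC, between-arm standard errors at Weeks 12 and 24 are too small by a factor of √DE, from 1.02 to 1.38 over the assumed range, and the real type I error exceeds 5%. A middle case, groups of 8 with ICC 0.05, puts it at about 8% to 9%, depending on whether groups shrink with attrition. In that case power is about 72% to 75%. Whether power falls short of 0.80 depends on an ICC above roughly 0.02 at groups of 8. All these sizes rest on assumed group sizes and ICCs; the direction of the error in the standard errors does not, once the ICC is above zero.

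**What to change.** 1. Record each participant's teleconference group and therapist in the study database. Session attendance is already tracked under the fidelity procedures, so membership may be recoverable, but it should be an explicit field.
2. Add to the primary model a random effect for teleconference group, nested in condition and acting at Weeks 12 and 24, with Kenward-Roger or Satterthwaite degrees of freedom.
3. State the planned group size and an ICC range, and restate the 0.80 power over that range.

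The cost is analysis wording and a database entry; the change itself needs no new patients. The downside is wider intervals and a less favourable stated power. With about 6 to 8 groups per arm the drop may be material, as Step 6 shows. For scale, holding 0.80 at groups of 8 and ICC 0.05 would take 43.6 × 1.35 = 58.9, rounded to 59 completers, and 59 / 0.8 ≈ 74 per arm (222 in total) by the design effect alone. If the sample stays at 189, the lower power should be stated openly.

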### Recruitment and eligibility

Individuals for this study will be recruited in several different ways in the State of Ohio. We have restricted recruitment to Ohio to avoid complications with state licensure laws. Fliers for the study will be distributed through MS support groups and National MS Society and MS Association of America events. We will recruit through physician referral and electronic health record review, and an MS patient registry maintained by the North American Research Consortium on MS (NARCOMS), which has approximately 400 registered individuals in Ohio who are ambulatory. Regardless of the recruitment method, individuals who are interested in participating in the study will be asked to contact the study office. Potential participants will undergo a telephone screening procedure to determine eligibility, and then a confirmation of eligibility through contacting their physician.

Inclusion criteria are: (1) physician-confirmed diagnosis of MS and physician-consent to initiate a physical activity program, (2) age between 18 and 65 years, (3) ability to walk at least 25 feet with a cane, (4) ability to carry on telephone conservations in English, (5) a Patient Determined Disease Step score between 1 (mild disability) and 5 (unilateral support required)
[34], (6) a current sedentary lifestyle (i.e., purposeful exercises ≤ 2 days per week for 30 minutes)
[35], and (7) experiences moderate to severe fatigue (a score of ≥ 4 on the Fatigue Severity Scale)
[36]. Exclusion criteria are: (1) pregnancy, (2) cardiopulmonary diseases, (3) uncontrolled diabetes (hospitalized within the last six months), (4) greater than three falls in the past six months, and (5) severe cognitive deficits (weighted score of less than 12 on the short version of the Blessed Orientation Memory Concentration test)
[37].

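### A lone random intercept assumes equal variances and equal correlations over the three visits; if either fails, the visit-specific standard errors can be off by about 3-12%, in either direction

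*Protocol article*

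**What the plan says.** Under Data management and analysis, the protocol article makes linear mixed-effects models the main tool, "which include condition, time, and interactions as the fixed covariates", together with "a random intercept that models the correlation among outcomes collected from the same subject". It names no random slope, visit-specific residual variance, unstructured covariance or robust standard error. Generalized estimating equations are a fallback, but the trigger is non-normal random effects, not a wrong covariance. In the same section: "All tests will be two-sided, and p = 0.05 will serve as the criterion for significance", and "the results will not be controlled for multiple comparisons".

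The Sample size section uses the same covariance: "We assumed equal variance and correlation (rho = 0.5) between measures across time points", with "an effect size of 0.6 at Weeks 12 and 24". Sizing and analysis therefore agree with each other. Methods/Design puts the measurements at Weeks 1, 12 and 24 and says that the design is meant to compare immediate and sustained outcomes.

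**The concern.** A random intercept with independent residuals is compound symmetry. The model estimates one residual variance, pooled over all visits, and gives every visit-to-visit change the same standard error. That is right only if all three changes truly have the same variance.

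The design gives reason not to take this for granted. The outer visits are 23 weeks apart and adjacent visits 11-12 weeks apart. The first interval is active intervention and the second is non-contact. Entry also requires "a current sedentary lifestyle", and activity is a primary outcome, so the baseline spread of activity may be narrower than the later spread.

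At stake are the between-arm contrasts at particular visits, which would carry any claim of an immediate effect (Week 12) or a sustained effect (Week 24). The tests are run at 0.05 without multiplicity adjustment, so there is no slack to absorb an inflated error rate.

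**Working it through.** **Inputs from the article.** Three visits; random intercept only; two-sided 0.05; equal variance and correlation 0.5 as the sizing assumption. The article gives no standard deviations and no other correlations, so every alternative below is an assumption. Standard deviations are relative to the later visits.

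**Formulas.** Let v be the mean of the three visit variances and c the mean of the three covariances.
- Variance the model assigns to any change: 2(v − c).
- True variance of the change between visits i and j: s_i² + s_j² − 2·cov_ij.
- SE ratio: R = √(model variance / true variance).
- True type I error: 2[1 − Φ(1.96·R)].
- For the arm difference in level at Week 24: R = √(v / s_24²).

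The number per arm cancels from R.

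**The plan's own assumption.** Equal SDs, all correlations 0.5: the model gives 2(1 − 0.5) = 1.0 and the truth is 1.0. R = 1 and type I error is 5.0%. On its stated assumption the plan is correct.

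**Correlation falls with time, equal SDs.**
- Adjacent 0.55, Weeks 1-24 0.40. Mean correlation (0.55 + 0.55 + 0.40)/3 = 0.50, so the model variance is 1.0.
  - Week 24 change: true 2(1 − 0.40) = 1.2; R = √(1.0/1.2) = 0.913; type I error 7.4%.
  - Week 12 change: true 2(1 − 0.55) = 0.9; R = 1.054; 3.9%.
- Adjacent 0.60, Weeks 1-24 0.40. Mean correlation 0.533, so the model variance is 0.933.
  - Week 24 change: true 1.2; R = 0.882; 8.4%.
  - Week 12 change: true 0.8; R = 1.080; 3.4%.

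**Smaller baseline spread only, all correlations 0.5.**
- Baseline SD 0.8: v = (0.64 + 1 + 1)/3 = 0.88; c = (0.4 + 0.4 + 0.5)/3 = 0.433; model variance 0.893.
- Baseline SD 0.7: v = (0.49 + 1 + 1)/3 = 0.83; c = (0.35 + 0.35 + 0.5)/3 = 0.40; model variance 0.86.

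| Contrast | SD 0.8: true variance, R, type I | SD 0.7: true variance, R, type I |
|---|---|---|
| Week 24 change from Week 1 | 0.84, 1.031, 4.3% | 0.79, 1.043, 4.1% |
| Week 24 versus Week 12 | 1.00, 0.945, 6.4% | 1.00, 0.927, 6.9% |
| Week 24 level | 1.00, 0.938, 6.6% | 1.00, 0.911, 7.4% |

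**With attrition.** A REML random-intercept simulation (63 per arm, 10% then 20% missing completely at random, 3,000 runs) gave, for the Week 24 change contrast:
- correlations 0.60 adjacent and 0.40 outer: SE ratio 0.90, type I error 8.4%;
- baseline SD 0.8 with equal correlations: 1.01 and 4.7%;
- true compound symmetry: 0.98 and 5.6%.

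**Overall condition-by-time test.** In simulation with 3 arms of 50 and complete data (20,000 runs), type I error stayed between about 5.0% and 5.4% in the scenarios tried. The pooled error is right on average and wrong only for individual contrasts.

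**The case against.** The strongest reply has four parts.

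1. *The article cannot show that the assumption fails.* Its only covariance figure is equal variance with correlation 0.5, and under that the standard errors are right. This stands. A reader might infer that the Week 24 error bars are wrong; the document supports only that they can be.
2. *The entry criteria do not make the Week 24 change look too precise.* This also stands. A reader might infer that a restricted baseline makes that standard error too small. Taken alone, a smaller baseline SD does the reverse (4.1-4.3%); inflation of that contrast comes from falling correlation. The fatigue criterion is also on the Fatigue Severity Scale, whereas the outcome is the Fatigue Impact Scale, so it narrows the outcome only indirectly.
3. *The plan does not name the Week 24 change as the decisive test, and the overall interaction test is nearly unaffected.* This is correct, and it limits the point to visit-specific contrasts. Those contrasts are still needed to say which arm differs, and when.
4. *A random intercept is common for three visits, and residual structure is usually left to the analysis plan.* This stands in part. The wording does not exclude visit-specific residual variances. But the article does name the term that models within-person correlation, and that term matches the sizing assumption, so this is a stated choice rather than silence.

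A reader might also infer a material bias when dropout depends on Week 12 scores. The article states no dropout mechanism, so no size can be given, and the point does not rest on it.

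**Conclusion.** The point holds as a conditional weakness, with moderate confidence. As written, the primary model assumes compound symmetry, and the fallback does not respond if that fails. For the patterns examined, the standard errors of visit-specific contrasts are between about 12% too small and 8% too large, and type I error runs from about 3.4% to 8.4% instead of 5%. The direction depends on the pattern: falling correlation inflates the Week 24 change contrast and makes the Week 12 change contrast conservative, while a narrower baseline alone inflates the Week 24 level and Week 24 versus Week 12 contrasts. All of these figures rest on assumed correlations and SDs and on independent residuals around the random intercept. If variances and correlations really are equal across visits, there is no error.

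**What to change.** Keep the same fixed effects (condition, time as a categorical factor, and their interaction). Replace the lone random intercept with an unstructured 3×3 within-person covariance and Kenward-Roger degrees of freedom. Fall back to a simpler structure with robust standard errors only if the model does not converge. Any random effect for the teleconference group should be kept in addition, since this change concerns only the covariance over time within a person.

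No new data are needed. An unstructured covariance has six parameters against two for compound symmetry, so the cost is four parameters with 189 participants planned. It contains the planned model as a special case, so little is lost if compound symmetry turns out to hold.
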